**Fig 1 Fig1:**
[figure not shown]
CONSORT flow diagram

In order to select the sample, a one-stage sampling method will be used. For this purpose, a list of secondary schools will be prepared. Then, out of 25 high schools, 8 will be randomly selected and screened for gaming disorder in all students who play computer games (both online and offline) using the nine-item Internet Gaming Disorder Scale - Short Form (IGDS-SF9). An online questionnaire will be provided to adolescent students through school information channels so that those who volunteer may participate in this research. Eligible adolescents (*n* = 206) will be randomly assigned into action control (*n* = 103) and intervention groups (*n* = 103). An online questionnaire will be provided to adolescent students through school information channels so that those who volunteer can participate in this research.

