### Sample size/power calculation

The sample size for the study was estimated based on a pilot study of 12 adolescents with IGD. The results of the pilot study showed that adolescents reported lower scores on the IGDS-SF9 at post-treatment follow-up (pre-treatment *M* = 34.59, *SD* = 16.91; post-treatment *M* = 25.37, *SD* = 17.94). However, 2 adolescents did not complete the post-treatment assessments. It is hypothesized that the app-based intervention will have at least a moderate mean effect size of 0.50 (Cohen’s *d*) compared to the control group. Using G*Power [61], sample size was calculated assuming a power of 90% for a two-group comparison analysis with three measures over time, the significance level of 0.05 and loss to follow-up of approximately 20%. The final sample size was set at 103 participants for each group.

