##### Primary outcome measure

The primary outcome measure will be the IGDS-SF9. The IGDS-SF9 assesses the severity of IGD in adolescents [6, 62]. These activities include any game, whether online or offline performed through consoles, computers, laptops, tablets, and smartphones. The IGDS-SF9 has 9 items correspond to the nine IGD criteria defined by the DSM-5. All items are rated a five-point Likert type scale from 1 (never) to 5 (always). The total score is obtained by summing all 9 responses and range from 9 to 45 with higher scores indicating a higher risk of developing IGD. The Persian version of the *IGDS-SF9* was found to be highly valid and reliably among Iranian adolescents [62].

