### Statistical analysis

A blinded biostatistician will analyze the data using SPSS version 25 and MLwiN version 2.27 software. An intention-to-treat analysis will be used to compare the intervention effects between the active control and intervention groups. The Kolmogorov–Smirnov test will be used to assess normality distribution of study variables. Multilevel linear models (MLMs) using a random-effects model will be conducted to compare primary and secondary outcome measures across the two groups over baseline and at 1 month and 3 months after the intervention. Within-group intraclass correlations will be calculated, and a two-level mixed model will be used with adolescents nested in time.

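### The Statistical analysis section states the levels of the primary model backwards; fitted as written, it would give wrong standard errors

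*Protocol article*

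**What the plan says.** The protocol names one primary outcome: "The primary outcome measure will be the IGDS-SF9". The Statistical analysis section gives the model for it: "Multilevel linear models (MLMs) using a random-effects model will be conducted to compare primary and secondary outcome measures across the two groups". Three occasions enter that model: baseline and the two follow-ups, at 1 and 3 months. The section adds that "Within-group intraclass correlations will be calculated" and then sets out the levels: "a two-level mixed model will be used with adolescents nested in time".

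That last phrase is the only place where the levels are defined. No other section names the adolescent as the random-effect unit. The Study design section and the description of the app's questionnaires both have each participant assessed at baseline and again at 1 and 3 months.

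**The concern.** In a two-level model the level-2 units carry the random effect that makes level-1 records correlated. Under the printed hierarchy the level-2 units are the occasions, three in all, and the level-1 records are adolescents. No term then links one adolescent's baseline score to the same adolescent's later scores. That link is the reason for using a repeated-measures model.

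The design does not fit that hierarchy either. Nesting adolescents in time would mean different adolescents at each occasion, whereas here the same adolescents return.

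At stake are the interval and p-value for the primary outcome. The direction of the error depends on the contrast tested, and the Statistical analysis section does not say which contrast carries the treatment effect.

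**Working it through.** **The plan's own figure.** The sample size section specifies "at least a moderate mean effect size of 0.50" (Cohen's d), "assuming a power of 90% for a two-group comparison analysis with three measures over time", a 0.05 significance level and about 20% loss. A plain two-sided comparison of two means at d = 0.5 and 90% power needs 86 per arm (noncentral t). 86 × 1.2 = 103.2, which matches the stated 103 per group. The match does not depend on the nesting, so correcting the hierarchy leaves the sample size alone.

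**Inputs for the check.**
- Occasions: 3, from the Statistical analysis section.
- Completers per arm: 103 × 0.8 = 82.4, taken as 82.
- Effect: a between-arm difference of 0.5 in change from baseline to one follow-up, in single-occasion SD units. Applying the protocol's d to change is an assumption.
- Test: two-sided 0.05 (sidedness is not stated).
- Within-person correlation ρ: not given in the protocol. Assumed 0.3, 0.5 and 0.7, equal between all pairs of occasions, with SD 1 at each.

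**Change (group-by-time) contrast.**
- True SE = √[(2/82) × 2(1 − ρ)].
- SE from the model as written = √[(2/82) × 2] = 0.2209, because ρ is ignored.
- Ratio, as written to true = 1/√(1 − ρ).
- Type I error = 2Φ(−1.96/√(1 − ρ)).
- Power, correct model = Φ(0.5/true SE − 1.96).
- Power, as written = Φ((0.5 − 1.96 × 0.2209)/true SE).

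| ρ | True SE | SE ratio | Type I error | Power, correct | Power, as written |
|---|---|---|---|---|---|
| 0.3 | 0.1848 | 1.20 | 1.9% | 77% | 64% |
| 0.5 | 0.1562 | 1.41 | 0.6% | 89% | 67% |
| 0.7 | 0.1210 | 1.83 | 0.03% | 99% | 71% |

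Example at ρ = 0.5: (0.5 − 0.4329)/0.1562 = 0.43, and Φ(0.43) = 0.67.

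**Group effect pooled over the three occasions.**
- Ratio, as written to true = 1/√(1 + 2ρ) = 0.79/0.71/0.65.
- Type I error = 2Φ(−1.96/√(1 + 2ρ)) = 12.1%/16.6%/20.6%.

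**Simulation.** Mixed models were fitted to null data with the random intercept placed on time or on the adolescent, with 63 to 72 replicates per ρ. With the intercept on time, the pooled effect was rejected in 10%/17%/25% of replicates and the change contrast in none. With the intercept on the adolescent, rejection rates were about 3% to 8%. With so few replicates this confirms the direction of the errors but not the exact rates.

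**The case against.** The strongest reply is that this is a slip of the pen. The same paragraph plans random-effects multilevel models over repeated assessments and the calculation of intraclass correlations, which points to an intention to model within-person correlation. Time as a random factor with three units also sits badly with its use as the axis along which the arms are compared. This is a fair reading and perhaps the likelier one. What stands of it is that the consequence is conditional on literal fitting.

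The reply does not settle the matter. The sentence on intraclass correlations never says that the group is the adolescent; under the printed hierarchy it would be the occasion. An analyst must declare the level-2 identifier to the software, and this sentence is the only instruction on it.

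The reply is also right that the pooled group effect is not named as the primary test. It would dilute any benefit with a pre-treatment score. The Objectives and the Statistical analysis section both compare the arms over time, so the change contrast is the natural test, and for that contrast the error is conservative.

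Three stronger readings might be inferred, and the documents do not support them:
- *Baseline is wrongly given the same variance as follow-up.* No variance structure is stated.
- *Baseline scores are cut off at the eligibility score of 32.* The Study design section has eligible adolescents complete baseline measures after eligibility is reviewed. Baseline may therefore be a separate administration from screening.
- *Leaving out school invalidates the test.* The protocol says that "out of 25 high schools, 8 will be randomly selected and screened for gaming disorder", but this only describes sampling. The Randomization section allocates individual adolescents 1:1 by simple randomization, so the error inflation of a cluster-randomized trial does not follow.

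**Conclusion.** The point holds as an error in the text with a conditional consequence. The hierarchy is printed the wrong way round in the one sentence that defines it, and the rest of the protocol does not correct it. This is a wrong statement about the primary model, so it cannot be put down to detail left for an analysis plan.

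If the sentence were followed literally, the main cost would be lost power on the change contrast: from 89% to 67% at ρ = 0.5, and from 77% to 64% or 99% to 71% at the ends of the assumed range. A reader might infer that the trial faces an inflated false-positive rate. That follows only if a group effect pooled over all three occasions were tested, which the protocol does not say.

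The sizes rest on the assumed ρ, equal correlation and variance across occasions, 82 completers per arm and a two-sided test. The reversal itself rests on none of these.

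**What to change.** In the Statistical analysis section, replace the phrase on levels with: *measurement occasions (level 1) nested in adolescents (level 2), with a random intercept for adolescent*.

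Add a sentence stating that the treatment effect on the IGDS-SF9 is the group difference at follow-up adjusted for baseline. This can be done with baseline IGDS-SF9 as a covariate or through the group-by-time contrast, and the sentence should say which. It should also name either 1 month or 3 months as the primary follow-up, since the protocol does not choose between them.

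The cost is two sentences, settled before the data are analysed. The sample size, data collection and named software stay as they are.

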## Discussion

The present study will aim to investigate the effectiveness of an educational intervention based on the TTM model and CBT in the treatment of IGD in adolescents. To the best of our knowledge, this study will be the first online intervention to aim to treat IGD and decrease the duration of online gaming and severity of IGD among adolescents. As described above, the present study uses a combination of TTM and CBT models for the intervention.

In general, cognitive, emotional, and physiological processes are involved in the development of addictions. These processes manifest in addictive behaviors. Therefore, theories and models of behavioral change have an important role in developing interventions [68, 69].

In the present study, in addition to using the CBT framework, the TTM is also used for developing the intervention. Using BCTs, the study attempts to increase motivation in adolescents in order to move from the early stages (i.e., precontemplation and contemplation) to later ones (e.g., maintenance). For people in the preparation and action stages, an attempt will be made to help them to the action and maintenance stages by using planning and increasing self-efficacy.

The app-based intervention was chosen for treating gaming disorder among adolescents for several reasons [1]. Despite help-seeking for a behavioral addiction typically being advantageous for affected people to obtain external assistance to facilitate dealing with the behavioral addiction, treatment-seeking is relatively infrequent in gaming disorder compared to other behavioral addictions [70]. Therefore, new modes of delivery (e.g., internet-based or app-based interventions) are warranted to increase dissemination. This approach is cost-effective and often easier to deliver compared to face-to-face delivery [2]. There is a concern for internet-related behavioral addictions with respect to internet-based modes of intervention (i.e., internet- or app-based interventions) may lead to worsening of the disorder in individuals. However, past studies have shown that such interventions can also be useful for internet-related behavioral addictions (including gaming addiction [71, 72]). Considering how people with internet-use concerns function with respect to internet use in general is important, particularly given the many aspects of daily life that involve internet use [3]. Due to the COVID-19 pandemic, many face-to-face interventions have shifted to online modes of delivery, given benefits that they offer.

The present study has some limitations. In the present study, only high-school students will be assessed. Therefore, the results of the study may not be generalized to younger age groups. Also, despite the use of a behavior-change model in the present study, the follow-up time (i.e., 3 months) to evaluate maintenance in students is relatively short. Nonetheless, the results of the present study should be useful to assess the efficacy of an online treatment for adolescents with IGD.

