### Study interventions

#### Intervention condition

The TTM model consists of six domains including (1) stages of change, (2) process of changes, (3) decisional balance, (4) change level, (5) self-efficacy, and (6) temptation. In this study, we will focus on three domains, as described below. The first domain is stages of change. While changing behavior and achieving the desired behavior, it is important to consider different stages [27]. In the first stage (Stage 1: Precontemplation), due to lack of awareness or knowledge or experiences of failed attempts to change in the past, the person may not have enough motivation to consider behavioral change during the next 6 months. In the next stage (Stage 2: Contemplation), the person has the necessary knowledge regarding the results of performing the desired behavior and knows the benefits of performing the behavior and the costs of performing the behavior, but he/she may not have self-confidence or motivations to make changes in behavior during the next 6 months. In the third stage (Stage 3: Preparation), people may analyze more fully costs and benefits in performing the behavior. People in this stage value the benefits more than the obstacles, and by planning for the next 30 days, they typically feel one step closer to their goals. After the preparation stage, the person may be better able to resist temptations and persevere to adopt the new behavior. In the next stage (Stage 4: Action), a new behavior may be adopted by the person within the next 6 months. In the next stage (Stage 5: maintenance), positive changes in his/her lifestyle have typically occurred, and he/she has experienced a change in behavior for at least 6 months and a maximum of 5 years with more confidence and less temptation. The risk of unusual temptations and the consequences of false self-confidence may still precipitate relapse.

The second domain of the TTM model involves processes of changes. These processes include overt and covert activities that a person may use to progress through the stages of change. In other words, these include any activities that a person does to help modify the way he/she thinks, feels or behaves.

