The next TTM domain considered is decisional balance. Decision-making is the process by which an individual considers the outcome of mental agreements (positive mental images, values, and beliefs) and oppositions to engage or not in behaviors. This domain is similar to that of perceived benefits and barriers in the health belief model [56]. The balance between perceived agreements and disagreements often fluctuates throughout stages of change.

Self-efficacy is the third domain considered for the intervention group. This domain, which comes from Bandura's theory of social learning, is a person’s self-efficacy and has a linear and positive relationship with the domain of stages of change. If a person goes to higher stage of change, his/her self-efficacy also increases [57].

The present study will focus on three domains of the TTM model (i.e., stages of change, self-efficacy and decision balance) in order to investigate the role of the TTM model in the treatment of IGD. One of the reasons for selecting these three domains is their success in statistically predicting individuals’ addictive gaming behaviors, which has been examined and demonstrated in a previous study [58].

Beside the TTM model, CBT will be used for our intervention. CBT is a form of psychotherapy that helps people understand thoughts and feelings that influence their behaviors. During treatment, a person learns how destructive or disturbing thoughts may have negative effects on their behaviors [59], and they may learn coping skills to manage their thoughts and feelings in a more healthy fashion [30].

After installing the app, each individual enters into the study with a use code that can be a mobile phone number or email that is recorded in the initial screening of each person in the study. Thereafter, a confirmation code is received via SMS.

The main page of the app consists of 4 sections: 1. content of training sessions, 2. exercises and weekly assignments, 3. questionnaires, and 4. a progress chart. The trainings are designed for 8 consecutive weeks (one session per week), and the approximate duration of each session is 30 min. Training includes written texts, videos, and audio files (relaxation music, relaxation exercise, and audio stories). Table 1 provides an overview of the content of each session in the intervention group (Screenshots of the app is provided in Additional file 1).

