##### Stage of Change Questionnaire (SOCQ)

Stage of change will be measured using a single item: “Did you play online games for 20 hours or more a week during last month?”. Reponses options are as follows: “A. Yes, and I do not plan to reduce my digital game use. B. Yes, and I plan to reduce my digital game use in the next 6 months. C. Yes, and I plan to reduce my digital game use in the next 30 days. D. Not this month, but I have played digital games for less than 20 hours a week in the past 6 months. E. No, and I have not played digital games more than 19 hours a week in the past 6 months. F. No, and I have NEVER played digital games more than 19 hours a week”.

Based on the answers given, the participants will be classified into one of the five stages of change described in the present study: A = (Precontemplation), B = (Contemplation), C = (Preparation), D = (Action), E = (Maintenance), and F = (A participant that is unlikely to be struggling from IGD) [58].

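### Adolescents in stages A to C at baseline cannot truthfully reach maintenance through the intervention by the last assessment, yet the stage rule counts every answer E as maintenance

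*Protocol article*

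**What the plan says.** The Intervention condition section describes a person in maintenance as someone for whom "he/she has experienced a change in behavior for at least 6 months and a maximum of 5 years". The Stage of Change Questionnaire (SOCQ) section measures stage with a single item whose stem is "Did you play online games for 20 hours or more a week during last month". Answers A, B and C (precontemplation, contemplation, preparation) all begin with Yes. Answer D is classed as Action. Maintenance is assigned to one answer: "E. No, and I have not played digital games more than 19 hours a week in the past 6 months". The classification uses the current answer only and is not checked against the baseline answer.

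On timing, the Intervention condition section states: "The trainings are designed for 8 consecutive weeks (one session per week". The Abstract gives the same course as 2 months. Questionnaires follow at 1 and 3 months after the course ends (Intervention condition, Statistical analysis).

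Stages of change are among the aims listed under Objectives, and the SOCQ is a secondary outcome. The Discussion says that the study tries to help adolescents "move from the early stages (i.e., precontemplation and contemplation) to later ones (e.g., maintenance"). It later lists as a limitation that "the follow-up time (i.e., 3 months) to evaluate maintenance in students is relatively short".

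**The concern.** A short follow-up usually means weaker evidence that a change lasts. Here the difficulty is one of definition. An adolescent who reports 20 hours or more a week at the start cannot, at the last visit, have had 6 months below that level that began with the intervention. The stage rule still labels any E from that adolescent as maintenance.

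Such answers are plausible. The printed wording of D and of E refers in both cases to play below 20 hours a week over the past 6 months, so an adolescent who cut down recently could pick E. Participants know their allocation (Randomization section), so such errors need not be equal in the two arms. A reader guided only by the stated limitation could take recorded moves from A, B or C to E as early evidence of maintenance.

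**Working it through.** **Inputs**
- Duration that defines maintenance: at least 6 months (Intervention condition); look-back of answer E: 6 months (SOCQ section).
- Course length: 8 weeks = 56 days (Intervention condition) or 2 months (Abstract). A third reading ends the course when session 8 opens, 7 × 7 = 49 days after session 1.
- Last assessment: 3 months after the course ends. This figure agrees between the Abstract, Study design, Intervention condition, Statistical analysis and Discussion.
- One month = 365.25 / 12 = 30.44 days.

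**Step 1. Time from first session to last assessment**

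Time = course length + 3 months; shortfall = 6 − time.
- 56 days: 56 / 30.44 + 3 = 1.84 + 3 = 4.84 months; shortfall 1.16.
- 2 months: 2 + 3 = 5.00 months; shortfall 1.00.
- 49 days: 49 / 30.44 + 3 = 1.61 + 3 = 4.61 months; shortfall 1.39.

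At the 1-month assessment the times are 2.84, 3.00 and 2.61 months, with shortfalls of 3.16, 3.00 and 3.39.

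**Step 2. What a truthful E would require**

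At the last assessment, the 6-month window of answer E opens 1.00 to 1.39 months before the first session. A truthful E therefore needs play below the threshold from at least a month before the intervention began. Such a change cannot be an effect of the intervention, whenever baseline was taken.

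**Step 3. Consistency with the baseline answer**

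If baseline is taken at the first session, answers A, B and C report 20 hours or more a week in the month just before it. The window of answer E (1.00 to 1.39 months back) covers that whole month, so the two answers contradict each other even if play fell on day 1.

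**Step 4. If baseline comes earlier**

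The article does not state the interval from baseline to first session. As an assumption, take the whole recruitment window under Trial status, 19 April to 31 May 2021: 42 days = 1.38 months. Baseline to last visit could then be 1.38 + 4.84 = 6.22 months. An E would no longer contradict the baseline answer, but step 2 still applies: the change would have begun before treatment.

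**Step 5. Follow-up that would be needed**

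For 6 months counted from the first session, the last assessment would have to come 6 − 1.84 = 4.16 months or more after an 8-week course. Counted from the end of the course, it would be 6 months.

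**The case against.** The strongest reply is that the article discloses the limitation itself, naming both the stage and the short follow-up, so that only wording remains. It adds that the objective is to compare stages of change, that maintenance appears only as an example in the Discussion, and that both arms face the same ceiling.

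Much of this stands, and it rules out several stronger readings.
- A reader might infer that the trial cannot observe maintenance at all. That is not so. Entry depends on the IGDS-SF9 score and not on hours played, so adolescents in Action at baseline can enrol, and they can reach maintenance within follow-up. Their share is not given.
- A reader might infer that a planned comparison of maintenance proportions is invalid. No such analysis is stated; the Statistical analysis section names multilevel models for all outcomes.
- A reader might infer that the absence of moves to maintenance would look like no effect. Moves from A to B, from B to C and into Action remain visible and belong to the stage comparison.
- A reader might infer that every E from a baseline A to C participant is a misreport. Step 4 of the working shows that this depends on when baseline is taken.

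What the reply does not answer is the classification rule. It labels as maintenance an answer that, for baseline A to C participants, cannot be both truthful and an effect of the intervention. Saying that follow-up is short does not tell the reader so. The shared ceiling does not help either, because the problem is recorded answers above it, and these may differ between unblinded arms.

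**Conclusion.** The point holds in a limited form. For adolescents in stages A to C at baseline, a truthful move to maintenance caused by the intervention cannot be observed at any planned assessment. The last one falls 4.84 months (8 weeks) or 5.00 months (2 months) after the first session, against the 6 required; the 49-day reading gives 4.61. This rests on the article's own 6-month definition, on reading answer E as printed, and on counting change caused by the intervention from the first session at the earliest. It does not depend on when baseline is taken.

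The consequence is confined to one secondary outcome and one subgroup. The IGDS-SF9 primary outcome, the sample size, the remaining stage movements and participants in Action at baseline are untouched. It is a correction to a classification rule and to two statements in the Discussion, not a flaw in the design as a whole.

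**What to change.** 1. Keep the ordered stages A, B, C and Action. For participants who were A to C at baseline, count a follow-up answer E as D, read as Action or beyond. The recode is to the Action stage as the article classifies it, since the printed wording of D carries a 6-month phrase of its own. Leave the classification unchanged for participants already in Action at baseline.
2. Reword the Discussion in two places, where maintenance is given as an example of movement from the early stages and where the length of follow-up is listed as a limitation. Both should say that maintenance cannot be shown within this follow-up for participants who were A to C at baseline.

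Do not collapse the outcome to D or E against A to C. That would discard the moves from A to B, A to C and B to C that the intervention is meant to produce, as well as the attainable move from D to E.

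The cost is small: the D/E distinction is lost for participants who were A to C at baseline. No visit, participant or instrument is added. The Trial status section says the trial has not yet started, so on that account the rule can be fixed before any data are seen. It uses only a participant's own baseline and follow-up answers, so it can be applied without knowledge of the arm.
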